# Synopsis

# Primary Objective

To compare the accuracy, reliability, and repeatability of the NIDEK Gonioscope GS-1 (NIDEK, Gamagori, Japan) with conventional gonioscopy and ultrasound biomicroscopy in evaluating the iridocorneal angle in glaucoma and glaucoma suspect patients.

# Study Duration

The study will continuously enroll patients until goal enrollment.

# Study Design

This is a prospective, non-randomized, cross-sectional, experimental study.

# Study Population

We aim to enroll patients diagnosed with glaucoma or who are glaucoma suspects. There will be no enrollment restrictions based on gender, ethnic origin or HIV status and the study population will reflect the demographics of NYU Department of Ophthalmology.

# Number of Participants

60 patients (120 eyes) will be enrolled in this study after an initial ad-hoc power calculation was performed to determine necessity to reach statistical significance.

# - Introduction

# Introductory Statement

The NIDEK Gonioscope GS-1 captures iridocorneal angle images using an optical gonioprism and a built-in image sensor without the use of mydriatic agents. Through the use of a built-in rotator unit, a color circumferential image of the iridocorneal angle and its peripheral area is captured. The captured image can be stored in the device’s internal memory, printed onto paper, or transmitted to external equipment.

# - Background

Gonioscopy is a vital part of the ophthalmologic examination, as it allows clinicians to evaluate the iridocorneal angle of the eye. The iridocorneal angle contains the orifice to the draining pathway of the aqueous humor from the anterior chamber into the canal of Schlemm. More acute, or “narrow,” angles can put patients at risk for glaucoma due to obstruction of the route of the fluid into the trabecular meshwork. Accumulation of pigment or inflammatory cells can also lead to obstructions of the drainage system and consequent increase in intraocular pressure. Gonioscopy allows clinicians to assess the width of the angle as well as look for any structural deformation or accumulation of material.

The goniolens is a specially designed lens to allow visualization of the angle that is placed on the patient’s cornea by the clinician during the ocular examination. When used in conjunction with a slit lamp, it gives the clinician a view of the iridocorneal angle, which is otherwise masked by the ocular configuration. Although it is considered the gold standard for assessment of the iridocorneal angle, gonioscopy can be difficult to perform. [1] The evaluation of the width of the iridocorneal angle is subjective and requires clinical experience. [1] As such, there is some inter-operator variability in the results obtained using this method.

Due to the time and skill required to obtain an accurate gonioscopic image on a conventional slit lamp, there has been interest in developing alternative methods to obtain quick, accurate, and reliable images of the iridocorneal angle. These alternative methods have involved the use of both new and existing technologies. For instance, currently available 3D Corneal and Anterior Segment Optical Coherence Tomography (3D CAS-OCT) has been used for this purpose. A study investigating the utility of 3D CAS-OCT in evaluating anterior segment parameters found a high degree of intra-grader repeatability, inter-grader repeatability, and correlation with conventional gonioscopy. [2]

With the goal of someday replacing conventional gonioscopy, a number of imaging devices have been developed specifically to assess anterior segment parameters. The Pentacam-Scheimpflug camera uses the Scheimpflug optical principle to photograph parts of the anterior segment that are not directly in line with the camera’s aperture. [3] The camera takes up to 50 slit images of the anterior segment in 2 seconds and uses software to construct a 3D image. [3] The benefit of this technology is that it requires little operator experience and begins scanning automatically once proper alignment has been achieved. [3] However, Pentacam-Scheimpflug only quantitatively estimates the width of the angle and does not directly visualize it. [3] It therefore cannot be used as a replacement for conventional gonioscopy.

Orbscan Scanning-Slit Topography is a technology that scans the entire surface of the cornea, the iris, and the lens using a slit-scanning beam. [3] By mapping both the posterior

surface of the cornea and the iris, Orbscan calculates an estimation of the iridocorneal angle. [3] However, like Pentacam-Scheimpflug, it does not directly visualize the angle. Paradigm P60 ultrasound biomicroscope can obtain images of the iridocorneal angle and has been used for decades in the form of A- and B-scans. [3] However, in order to obtain an image, it requires direct contact with the eye, which is uncomfortable for the patient, and is highly operator- dependent. [3]

The clinical utility of an imaging device that can produce quick, accurate, and reliable images of the iridocorneal angle is clear. If the NIDEK Gonioscope GS-1 can produce images that are of comparable quality to digital images obtained from a goniolens and slit lamp, it has the potential to increase the speed of clinical examination in glaucoma clinics and improve workflow by replacing conventional gonioscopy.

# - Rationale/Significance

# Problem Statement

Although gonioscopy plays an important role in glaucoma diagnosis and treatment, repeatability and reliability are user-dependent when a conventional goniolens is used. Furthermore, during examination, the goniolens must be manipulated to a significant degree to obtain full visualization of the iridocorneal angle. This study evaluates the reliability and accuracy of NIDEK Gonioscope GS-1 in obtaining images of the iridocorneal angle. The NIDEK Gonioscope GS-1 captures 360° images of the anterior segment, including the iridocorneal

angle, using a light source, multi-mirror prism, and a sensor. This device does not require use of a slit lamp nor manipulation of a goniolens.

# Potential Risks

Because the multi-mirror prism touches the surface of the eye it carries a risk of infection. We will perform high level disinfection or low temperature sterilization (EOG sterilization) after any use of the prism to reduce this risk. Additionally, all exposed surfaces near the eye, as well as the chin rest and forehead rest of the instrument, will be cleaned with alcohol before participants are examined. The multi-mirror prism is made from cycloolefin polymer (COP) resin. *In vitro* cytotoxicity assays found that concentrations of up to 100% COP did not obstruct colony formation of V79 Chinese hamster lung cells. Ocular irritation tests showed that COP does not irritate the cornea, iris, or conjunctiva of rabbits.

The prism may cause a foreign body sensation to the patient during the capture of iridocorneal angle image which may cause some discomfort.

Ultrasound biomicroscopy is an FDA-approved technology that uses an ultrasound probe to visualize intraocular structures, including the iridocorneal angle. The ultrasound probe does not directly contact the eye, but rather a balloon filled with water is put in contact with the eye. The probe contacts the water balloon. There is risk of some minor patient discomfort during ultrasound biomicroscopy.

# - Study Objectives Primary Objective

To compare the accuracy, reliability, and repeatability of the NIDEK Gonioscope GS-1 (NIDEK, Gamagori, Japan) with ultrasound biomicroscopy and conventional gonioscopy in evaluating the iridocorneal angle in glaucoma or glaucoma suspect patients. Repeatability refers to the ability of 2 separate ophthalmologists to identify the same iridocorneal angle width from each NIDEK image.

# Primary Outcome Variables

Images obtained by the NIDEK Gonioscope GS-1 will be compared with ultrasound biomicroscopy images and digital gonioscopic images obtained using a goniolens and slit lamp to determine if the NIDEK Gonioscope GS-1 can accurately and reliably capture relevant findings. To determine the accuracy of the NIDEK Gonioscope GS-1, we will use ANOVA to determine if the iridocorneal angle measurements obtained from the NIDEK Gonioscope GS-1 are statistically similar to measurements obtained from ultrasound biomicroscopy and standard gonioscopy. To determine inter-observer reproducibility when using this device, two observers will examine each image obtained from NIDEK Gonioscope GS-1 and separately determine the iridocorneal angle. Inter-observer reproducibility will be determined using Kappa's statistics and intraclass correlation coefficient. Lastly, we will determine if the time it takes to obtain images from the NIDEK Gonioscope GS-1 is statistically different from the time it takes to obtain images by conventional gonioscopy. This will be done via ANOVA.

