# - Methods

# Study Procedure

Subjects who meet eligibility criteria will be identified by study team and will be consented for the study. During their usual ophthalmology visit, all subjects will undergo conventional gonioscopy, ultrasound biomicroscopy, and gonioscopy with NIDEK Gonioscope GS-1. The NIDEK Gonioscope GS-1 will only be used on patients who are in the study. The experimental part of the visit using the NIDEK Gonioscope GS-1 should take approximately 10 minutes,

For conventional gonioscopy, the clinician may obtain digital images of the iridocorneal angle using a slit lamp and goniolens. For ultrasound biomicroscopy, the clinician may obtain ultrasound images that will then be stored within the biomicroscope device. For gonioscopy with NIDEK Gonioscope GS-1, the device may obtain and store images of the iridocorneal angle.

Following collection of the images, one ophthalmologist may examine images obtained from conventional gonioscopy and determine the width of the iridocorneal angle. The same ophthalmologist will determine the width of the iridocorneal angle from the ultrasound biomicroscopy images. This ophthalmologist will be masked to patient names and diagnoses. A second and potentially third ophthalmologists may examine images obtained from NIDEK Gonioscope GS-1 and determine the width of the iridocorneal angle. These ophthalmologists will also be masked to patient names and diagnoses.

Statistical analysis will be performed to determine the association between the findings of iridocorneal angle width in conventional gonioscopy images, ultrasound biomicroscopy images, and NIDEK Gonioscope GS-1 images of each patient. Further statistical analysis will be performed to determine the inter-observer repeatability of the findings of the two ophthalmologists who examined the images from NIDEK Gonioscope GS-1.

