# Primary Analyses

The analysis of the width of the iridocorneal angle will be done according to both the Scheie and Shaffer grading systems. Relationships between results obtained from conventional gonioscopy, ultrasound biomicroscopy, and NIDEK Gonioscope GS-1 will be evaluated by linear and quadratic models, as well as more advanced statistical methods.

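### The accuracy rule is an ANOVA on device means, so a GS-1 that is right on average but wrong in individual eyes passes

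*Protocol*

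**What the plan says.** The primary objective (protocol, Study Objectives) includes accuracy of GS-1 against UBM and conventional gonioscopy. Primary Outcome Variables states how accuracy is judged: "To determine the accuracy of the NIDEK Gonioscope GS-1, we will use ANOVA", the question being whether GS-1 measurements "are statistically similar to measurements obtained from ultrasound biomicroscopy and standard gonioscopy". No margin, limit of agreement or per-eye criterion is attached.

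Agreement statistics appear in the same section for a different purpose: "Inter-observer reproducibility will be determined using Kappa's statistics and intraclass correlation coefficient". That is agreement between two people reading the same GS-1 image, not between GS-1 and a comparator.

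The data are paired, since "all subjects will undergo conventional gonioscopy, ultrasound biomicroscopy, and gonioscopy with NIDEK Gonioscope GS-1" (Study Procedure). Angle width is an ordinal grade: the analysis "will be done according to both the Scheie and Shaffer grading systems" (Primary Analyses).

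Two other between-device analyses are mentioned. Study Procedure says "Statistical analysis will be performed to determine the association between the findings of iridocorneal angle width", and Primary Analyses says the relationships "will be evaluated by linear and quadratic models, as well as more advanced statistical methods". Neither is called the accuracy assessment and neither has a success criterion. Number of Participants sizes the study on a Cohen's kappa of 0.34 between manual gonioscopy and GS-1, but Primary Outcome Variables does not use that statistic for accuracy.

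**The concern.** The Background gives the hoped-for use as a device that could "improve workflow by replacing conventional gonioscopy". For that use, accuracy means the right grade in the individual eye. A comparison of device means answers another question: whether GS-1 reads wider or narrower on average. A device that misses narrow angles and invents them equally often has the right mean and would be declared accurate.

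This is a separate matter from treating a non-significant test as proof of similarity. Adding an equivalence margin for the mean difference would repair that weakness and leave this one untouched, because the quantity tested is still the mean.

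**Working it through.** **Inputs from the protocol.** Three methods on the same eyes; ordinal grades; 94 evaluable eyes, 120 enrolled from 60 participants; 5% type I error.

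**The plan's own figure.** With a null kappa of 0 and two equally likely categories, n = (z_α + z_β)² / κ². Two-sided this is (1.960 + 0.842)² / 0.34² = 67.9, so 68 eyes; one-sided it is 53.5, so 54. A null kappa of 0.05 (two-sided) gives 93.1, so 94. The protocol states no null kappa, so 94 can be neither confirmed nor refuted. The allowance for unreadable images is consistent: 94/0.8 = 117.5, so 118, within 120. None of this affects the present point; 94 is used below only as the number of eyes.

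**Algebra.** Let x_ij be the grade of eye i by device j, with n eyes and k = 3 devices.

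- Device sum of squares: SS_dev = n Σ_j (x̄_.j − x̄_..)². It depends on the device means only.
- One-way error: SS_w = Σ_j Σ_i (x_ij − x̄_.j)². It depends only on the set of values within each device.
- One-way F = [SS_dev/(k−1)] / [SS_w/(k(n−1))]. Reassigning GS-1 grades to other eyes changes neither term, so F is identical.
- Repeated-measures error: SS_w − SS_eyes, with SS_eyes = k Σ_i (x̄_i. − x̄_..)². Reassignment leaves SS_dev and SS_w alone. Where the devices track each other, it lowers SS_eyes, so the error term grows and F falls. Scrambling the grades makes a finding of similarity more likely.

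In one test data set with a shifted GS-1, the one-way F was 4.211 both before and after shuffling, while the repeated-measures p-value moved from 1.3 × 10⁻⁹ to 0.0025.

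**Simulation A.** Assumptions: 94 eyes; grades 0–4 with shares 5/10/15/30/40%; each reading off by one grade in up to 20% of eyes; three modalities; 3,000 to 4,000 runs per scenario. Pass means ANOVA p > 0.05. The last row comes from two separate sets of runs.

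| GS-1 | Exact agreement | Kappa vs gonioscopy | One-way pass | Repeated-measures pass |
|---|---|---|---|---|
| Good | 73% | 0.63 | 99.8% | 95.5% |
| Fully shuffled | 28% (35% off by ≥2 grades) | 0.00 | 99.7–99.9% | about 100% |
| One third (32 of 94) shuffled, gonioscopy error-free | not tabulated | not tabulated | 97.5–97.9% | 99.9% |
| Drawn independently of the patient, same shares | not tabulated | not tabulated | 96–97% | 91–93% |

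**Simulation B.** Different assumptions: latent width mean 2 and SD 1, two correlated eyes per patient, reading error SD 0.3 unless stated, rounded to grades 0–4; 94 eyes, 3,000 runs.

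| GS-1 | Exact agreement | Kappa | One-way pass | Repeated-measures pass |
|---|---|---|---|---|
| Good | 68% | 0.56 | 100% | 94% |
| Noisy, unbiased (error SD 1.0) | 40% | 0.21 | 100% | 94% |
| Shuffled | 27% | 0.00 | 100% | 100% |
| Precise, shifted by 0.25 grade | 63% | 0.50 | 91% | 1% |

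The noisy device passes as often as the good one. In repeated-measures form the slightly shifted but precise device (kappa 0.50) almost always fails, while the shuffled device (kappa 0.00) always passes. Kappa separates the good, noisy and shuffled devices; ANOVA does not.

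**The case against.** **Other between-device analyses are planned.** The association analysis and the linear and quadratic models would expose fully shuffled grades: under the assumptions of Simulation A the regression slope was significant in only about 5% of runs. That is correct, but the protocol attaches no accuracy criterion to them, and association is not agreement. A GS-1 reading a constant amount too wide would fit a line perfectly. The between-device kappa is used for sizing only; that the study was sized on it is a reason to use it for accuracy too.

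**The result depends on the means being close.** This stands as a limit. Shuffled grades with half the readings also lowered by one grade passed in only 9% (one-way) and 2% (repeated-measures) of runs. ANOVA does detect a sizeable systematic shift.

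**Permuting fixes the mean and inflates the pass rate.** This is partly right. Grades drawn independently of the patient pass slightly less often (96–97% and 91–93%), which does not change the conclusion.

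**A shuffled device is not realistic.** It is a limiting case showing that the test carries no information on individual eyes. The noisy, unbiased device in Simulation B is a plausible failure and passes as often as the good one.

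**A SAP may add agreement measures.** It may, but it would have to override an explicit statement in the protocol, which would still need amending.

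**Conclusion.** The concern holds. As written, the accuracy rule tests whether device means differ, whichever form of ANOVA is used, and cannot tell an accurate GS-1 from one that is wrong in individual eyes but right on average. With equal means, a device with no agreement beyond chance passes in over 99% of trials when grades are shuffled, and in at least 91% when grades are drawn independently of the patient.

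The percentages rest on assumed grade distributions and error rates, and two quite different sets of assumptions lead to the same conclusion. The invariance of the one-way F rests on no assumption. Because the rule governs a component of the primary objective and can give the wrong answer, it should be changed before GS-1 is compared with the other methods.

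**What to change.** In Primary Outcome Variables, replace the ANOVA criterion with a per-eye definition of accuracy based on the paired GS-1 and conventional gonioscopy grades:

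- the proportion of eyes with the same grade and the proportion within one grade;
- weighted kappa;
- the distribution and limits of the within-eye difference.

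Give each a 95% confidence interval that allows for two eyes per patient, and state in advance the agreement that would count as accurate. The within-one-grade proportion should not stand alone: in Simulation A the fully shuffled device would score 100% − 35% = 65% on it.

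Report the same measures against UBM where a common scale exists. Keep the mean difference, or the ANOVA, only as the measure of systematic bias. Align Study Procedure and Primary Analyses with this definition so that the association and regression models are clearly supportive. Using kappa for accuracy would also match the basis of the sample size.

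The cost is a protocol amendment and a modest amount of extra analysis. The paired grades are already to be collected, so no new data are needed.

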# Number of Participants

Following a preliminary data collection, we were able to estimate the sample size needed to reach statistically significant results. Assuming that the manual gonioscopy and automated gonioscopy GS-1 have an equal probability of recording a diagnosis, Cohen's Kappa of 0.34 was measured. To detect a fair agreement between the two modalities, while achieving 80% power and 5% type I error, we will need to collect data from 94 eyes. To account for the portion of images that are uninterpretable due to poor quality (10-20%), we asses a total of 120 eyes (60 participants) would be satisfactory for us to estimate the GS-1 as a diagnostic tool accurately.

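### GS-1 accuracy rests on an ANOVA finding the methods statistically similar, with no margin; a non-significant difference in means shows neither similarity nor eye-level agreement

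*Protocol*

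**What the plan says.** The objective in Protocol section 4.1 is "To compare the accuracy, reliability, and repeatability of the NIDEK Gonioscope GS-1" against UBM and conventional gonioscopy.

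Section 4.2 (Primary Outcome Variables) assigns a method to each part:

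- Accuracy: "we will use ANOVA to determine if the iridocorneal angle measurements obtained from the NIDEK Gonioscope GS-1 are statistically similar to measurements obtained" with UBM and standard gonioscopy. No margin, limit of agreement or minimum kappa is given.
- Two observers reading the same GS-1 images: "Inter-observer reproducibility will be determined using Kappa's statistics and intraclass correlation coefficient".

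Two other sections describe comparisons between the methods. Section 6.1 (Study Procedure) says: "Statistical analysis will be performed to determine the association between the findings of iridocorneal angle width" across the three methods. Section 6.7 (Primary Analyses) says that angle-width analysis "will be done according to both the Scheie and Shaffer grading systems", and that relationships between the methods "will be evaluated by linear and quadratic models, as well as more advanced statistical methods".

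Section 5.3 (Number of Participants) uses a different quantity. It reports that for manual gonioscopy and GS-1 "Cohen's Kappa of 0.34 was measured", and sizes the study to detect fair agreement between these two: "while achieving 80% power and 5% type I error, we will need to collect data from 94 eyes".

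**The concern.** ANOVA tests whether mean grades are equal. With no margin, the only result that could be reported as similar is failure to reject. This has two consequences.

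First, failure to reject becomes more likely with fewer eyes or noisier readings, so weaker data make the favourable conclusion easier to reach.

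Second, means carry no information on whether an individual eye gets the same grade from GS-1 as from the reference. That is what accuracy has to mean for a device that the Background hopes could replace conventional gonioscopy.

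The study could therefore report GS-1 as accurate with no eye-level agreement behind the statement.

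**Working it through.** **1. The plan's own figure.** The 94 eyes relate to a between-modality kappa, not to the ANOVA. For a binary rating at 50% prevalence, n = [(z_a·√Q0 + z_b·√Q1)/(k1 − k0)]².

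- Put k0 = 0, k1 = 0.34, two-sided 5%, 80% power. Then Q0 = 1. Observed agreement is 0.5 + 0.34 × 0.5 = 0.67, so Q1 = 0.67 × 0.33/0.25 = 0.884.
- n = [(1.96 + 0.842 × 0.940)/0.34]² ≈ 65.5.
- Section 5.3 states neither the null kappa nor sidedness. A null near 0.05 gives about 93, and 0.34 against 0.60 gives 93.7. The figure of 94 can be neither confirmed nor called wrong.
- 94/(1 − 0.20) = 117.5, so 120 eyes is consistent with the stated image loss.

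What matters here is that the study is sized on one quantity and judges accuracy by another.

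**2. A device with zero agreement.** Three methods were simulated on a 0–4 grade at 94 and 120 eyes, 2,000 runs each, alpha 0.05. The protocol gives none of the following, so all are assumptions: grade proportions 5/10/25/35/25% (SD 1.1), latent correlation 0.8 between the two references, independent eyes. GS-1 was given zero correlation with both references (kappa 0.00). Percentage of trials non-significant:

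| Mean offset of GS-1 (grades) | Repeated-measures ANOVA, 94 / 120 eyes | One-way ANOVA, 94 / 120 eyes |
|---|---|---|
| 0 | 92.8 / 93.7 | 96.0 / 97.4 |
| 0.1 | 87.3 / 85.8 | 92.4 / 91.6 |
| 0.2 | 70.8 / 64.0 | 80.2 / 74.2 |
| 0.3 | 46.6 / 35.6 | 58.3 / 49.0 |
| about 0.5 | 8.2 / 3.2 | 13.8 / 6.4 |

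The first row is essentially 1 − alpha = 95%, as for any valid test of means when the means are equal.

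**3. A device with good agreement.** With latent correlation 0.95 among all three methods (kappa about 0.6) and a 0.2-grade offset, repeated-measures ANOVA is non-significant in 1.7% (94 eyes) or 0.2% (120 eyes) of trials. The zero-agreement device with the same offset is non-significant in 70.8% or 64.0%. By this criterion the worse device looks more similar.

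**4. Which ANOVA.** Take 96 eyes (120 × 0.80), a true 0.3-grade GS-1 shift, and assumed eye SD 1.1 and reading SD 0.5.

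- The between-method sum of squares due to the shift is 96 × 0.3² × 2/3 = 5.76.
- Repeated measures removes eye variation. Non-centrality is 5.76/0.25 = 23.0, and the shift is missed in under 1% of trials.
- One-way leaves eye variation in the error term (1.21 + 0.25 = 1.46), and simulation gives about 83% missed.

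**5. Association.** Suppose the reference is uniform on grades 0–3 and GS-1 reads every eye one grade higher.

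- Correlation is 1.00.
- Exact agreement is 0 and chance agreement is 3 × (1/4 × 1/4) = 3/16, so kappa = (0 − 3/16)/(1 − 3/16) = −0.23.
- A fitted regression has slope 1 and intercept 1, so the offset shows in the intercept but not in the correlation.

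**The case against.** The best defence is that the plan should be read as a whole. Section 5.3 sizes the study on a between-modality kappa, and section 6.7 adds regression models and unspecified further methods. Taken together, these would catch the extreme cases. With 96 independent eyes, a random device combined a non-significant ANOVA with a significant positive association with both references in only 0.1% of runs. The constant one-grade shift in step 5 was never non-significant, even on one-way ANOVA. What does not stand is that this rescues the accuracy rule. No section makes accuracy depend on the models or combines them with the ANOVA, and section 4.2 ties accuracy to ANOVA alone. An SAP could add agreement statistics, but the protocol has already fixed this rule.

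A reader might infer more than the document supports:

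- That the plan ignores between-modality agreement altogether. Section 5.3 shows otherwise. The gap is that its kappa is not carried into sections 4.2, 6.1 or 6.7, and that UBM has no agreement statistic.
- That the linear models cannot see a constant offset. A correlation cannot; an intercept can.
- That the ANOVA ignores pairing within an eye. The protocol does not say whether it is one-way or repeated-measures, so the 83% in step 4 is conditional on one-way.
- That any useless device would usually pass. This needs a small mean offset, up to about 0.2 grade under the assumed SD. At half a grade it would usually be detected.

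**Conclusion.** The point holds and should be corrected before analysis. The accuracy part of the primary objective is tied to a test of means with no margin, so a non-significant result would be read as accuracy. The protocol does not spell out that reading, but none other is available from an ANOVA without a margin.

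The logical flaw and the roughly 95% rate for a zero-agreement device with equal means do not depend on the assumed SDs. The rates at non-zero offsets, and the one-way versus repeated-measures contrast, depend on assumed grade distributions, SDs and independent eyes. They illustrate size and are not predictions for this trial.

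**What to change.** In sections 4.2 and 6.7:

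- Stop treating a non-significant ANOVA as evidence of accuracy.
- Make the accuracy analysis an agreement statistic suited to ordinal grades, for GS-1 versus gonioscopy and for GS-1 versus UBM. Weighted kappa is one option and is consistent with section 5.3; other ordinal agreement measures would also serve. Give 95% CIs that account for two eyes per patient.
- Add the mean paired grade difference with its 95% CI. Claim similarity only if that interval lies within a margin the sponsor fixes before results are seen.
- Keep the linear and quadratic models as descriptive.

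The cost is revised wording and modest analysis code, with no new data. The sponsor must commit to a margin, and similarity becomes harder to claim. Precision will be moderate: with 94 eyes treated as independent, a binary rating at 50% prevalence and kappa 0.34, the standard error is √(0.884/94) = 0.097, giving a 95% CI of about 0.15 to 0.53. Correlation between the two eyes of a patient would usually widen it.

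### Accuracy is to be shown by an ANOVA finding readings similar, with no margin, so the chance of accepting a biased GS-1 is uncontrolled

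*Protocol*

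**What the plan says.** The primary objective (section 4.1) is "To compare the accuracy, reliability, and repeatability of the NIDEK Gonioscope GS-1" against ultrasound biomicroscopy and conventional gonioscopy. Section 4.2 then assigns a method to each part.

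- **Accuracy:** "we will use ANOVA to determine if the iridocorneal angle measurements obtained from the NIDEK Gonioscope GS-1 are statistically similar to measurements". The comparators are the "measurements obtained from ultrasound biomicroscopy and standard gonioscopy".
- **Reader agreement:** "Inter-observer reproducibility will be determined using Kappa's statistics and intraclass correlation coefficient". This concerns two observers reading the same GS-1 images.
- **Imaging time:** ANOVA again, this time to look for a difference.

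Section 6.1 (Study Procedure) adds an analysis of association between the three methods. Section 6.7 (Primary Analyses) names the Scheie and Shaffer systems and adds linear and quadratic models with further unnamed methods. None of these sections states an acceptable difference, limits of agreement or a confidence-interval criterion.

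The sample size (section 5.3) rests on a different quantity, the kappa between manual gonioscopy and GS-1: "Cohen's Kappa of 0.34 was measured" and, "while achieving 80% power and 5% type I error, we will need to collect data from 94 eyes". The total is 120 eyes of 60 participants, to allow for 10-20% unusable images.

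**The concern.** An ANOVA can give evidence that methods differ. It cannot give evidence that they agree, because a non-significant F also arises from too few eyes or noisy grading. Section 4.2 asks the same test to establish a difference for imaging time and similarity for angle width. It can do only the first.

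The error that matters for accuracy is declaring a biased GS-1 similar. Under this approach that is the ANOVA's type II error. A 5% significance level does not limit it, and no power or target difference for the ANOVA is given. The accuracy result would then lean towards the favourable answer as the data get worse. A result reached that way would be weak support for accuracy, which is part of the primary objective.

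**Working it through.** **1. The plan's own figure.** The only sized analysis is the kappa, at 94 eyes. With 50/50 marginals, n = [(z_a√(1−k0²) + z_b√(1−k1²))/(k1−k0)]². Putting in k1 = 0.34, k0 = 0 and 80% power gives 65.5 (66 eyes) two-sided and 51.3 (52) one-sided. A null kappa near 0.09 one-sided gives 94.5. The 94 is therefore not reproduced from the stated inputs, but it is not shown to be wrong, because the null value and the number of categories are not given. The inflation is consistent: 94/0.8 = 117.5, against 120 enrolled. Below, 94 serves only as the planned number of evaluable eyes.

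**2. Assumptions, since the protocol gives none.** Three methods, GS-1 shifted by δ grades, the two comparators equal, SD σ, eyes independent, α = 0.05.

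**3. Chance of a non-significant ANOVA.** The deviations from the overall mean are 2δ/3, −δ/3 and −δ/3. Their squares sum to (4+1+1)δ²/9 = (2/3)δ², so λ = (2/3)·n·(δ/σ)² with 2 and 3(n−1) degrees of freedom. For n = 94, δ = 0.25, σ = 1.0: λ = 62.67 × 0.0625 = 3.92. The 5% critical value of F(2, 279) is 3.03, and the chance of falling below it is 0.596.

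| True shift | SD 0.8 | SD 1.0 | SD 1.3 |
|---|---|---|---|
| 0.25 grade | 41% | 60% | 75% |
| 0.5 grade | 0.4% | 5% | 22% |

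A repeated-measures ANOVA with the same residual SD gives nearly the same values (for SD 1.0, 59.8% and 5.0%), so the result does not depend on an unpaired analysis. If the two eyes of a patient carried the same information, 94 eyes would act like 94/2 = 47. The repeated-measures rates at residual SD 1.0 would then be 78% and 31%.

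**4. Right mean, poor agreement.** With no mean shift the ANOVA is non-significant 95% of the time by construction, however badly GS-1 and the comparator disagree eye by eye.

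**5. An interval criterion on the same footing.** Take an illustrative margin of 0.5 grade. If the true shift equals the margin, the 90% interval lies inside it at most 5% of the time, whatever the noise. For an unbiased device, the half-width at 94 eyes is 1.661 × SD/√94, where SD is that of the within-eye difference. Power is approximately the chance that the observed mean lies within 0.5 minus that half-width.

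| SD of difference | Half-width | Standard error | Power |
|---|---|---|---|
| 1.0 | 0.171 | 0.103 | about 99.8% |
| 1.41 | 0.242 | 0.145 | about 92% |
| 2.0 | 0.343 | 0.206 | about 55% |

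A per-method residual SD of 1.0 corresponds to a difference SD of √2 × 1.0 = 1.41, so the middle row is the one to set against the SD 1.0 column in step 3.

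**The case against.** Several points on the other side are fair.

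- **The rule is inferred.** The protocol nowhere writes that a non-significant result means the device is accurate. That is true, but a test of equality without a margin offers no other route to similarity.
- **Other analyses exist.** The study was sized on a between-method kappa, and section 6.7 relates the three methods. However, section 4.2 does not use that kappa to judge accuracy, and association or regression models without a limit do not bound bias.
- **The analysis plan may add a margin.** It may, but section 4.2 names the test and what it is to show. The criterion is fixed, and fixed badly, rather than left open.
- **At the planned size a large bias is usually seen.** With 94 eyes and SD up to 1.0, a half-grade shift is missed in 5% of trials or fewer. This stands and limits the claim.

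Some stronger readings are not supported. A reader might infer that any imprecision makes GS-1 look better throughout. It does so only in the ANOVA, since noisy GS-1 reading would lower the inter-observer kappa and ICC. A reader might illustrate the flaw at 20 or 30 eyes, where most half-grade shifts are missed, but the plan is for 94 evaluable eyes. A reader might also take the 5% type I error in section 5.3 as a claim to control the ANOVA. It belongs to the kappa calculation.

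**Conclusion.** The concern holds. Section 4.2 rests part of the primary objective on a test that cannot establish it, and the chance of accepting a biased GS-1 is set nowhere. How large that chance is cannot be known from the protocol. On the assumed values it runs from 0.4% to 75%, driven by the shift and the SD. The direction needs no such assumption: for a given true shift, more noise or fewer eyes makes a finding of similarity more likely.

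Two further conclusions would go too far. The documents do not show that a biased device will pass. Nor do they show that an equivalence criterion could be met with no extra patients: that holds at a difference SD of 1.0, but power is about 92% at 1.41 and about 55% at 2.0, and with 55 effective eyes at SD 1.41 it is about 66%. No SD is given that would settle which applies.

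**What to change.** In section 4.2, replace the ANOVA similarity criterion with within-eye agreement of GS-1 against each named comparator, conventional gonioscopy and ultrasound biomicroscopy, separately for Scheie and Shaffer grades. For each:

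- Report the mean within-eye difference with its 90% confidence interval. Claim similarity only if the interval lies wholly inside a margin that the sponsor sets before grading, with a margin for each grading system.
- Report an eye-level agreement measure (weighted kappa, or limits of agreement) with its confidence interval. A mean difference alone lets over- and under-grading cancel.
- Calculate all intervals with allowance for two eyes per patient.
- Treat a non-significant ANOVA as inconclusive.

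The protocol should also say which of these comparisons must pass. The power figures above are for one comparison, and requiring several lowers them.

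The change needs new wording and pre-set margins, and no new procedures. The price is that a wide interval can no longer be reported as success, and an inconclusive result is possible with 94 eyes. The preliminary data behind the kappa of 0.34 may allow the SD of the differences to be estimated, which would show beforehand how likely that is.
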